### Outcome measures and assessors

#### Baseline data

Participant characteristics will be collected from (i) interview with parents (heredity for atopic diseases, passive smoking habits, duration of the infection) and (ii) medical record (gender, age, possible viral agent: respiratory syncytial virus or influenza).

To collect the main data, the nursing staff will make a clinical assessment at study start (t1) and the second assessment 20 min later (t2), following directly after the intervention/interval. See also Fig. 1. The same person will perform these two assessments. The following assessments will be performed every three hours for the rest of the infant’s hospital stay. They will be performed by the clinical staff available at that time. In the intervention groups, it will be a different member of staff who will perform the intervention from the one who makes the first two assessments. All members of the staff will be trained on how to perform the assessments, which in many aspects are identical to the standard protocol at the ward. Once daily, the clinical staff will report if the infant has received any inhalations (in which case the medical record is scanned for more information on this) and also if the infant is actively moving about in the room or not. See Additional file 2 for the assessment protocol in Swedish.

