### Randomisation

When a child is included in the study, it will be individually randomised to one of the three groups. A statistician who is independent of the study has performed randomisation in blocks, stratified by the two sites. The statistician prepared sealed paper envelopes, numbered in sequence, that are kept in a locked safe accessible only for the researchers responsible for the study. A small number of envelopes will be brought to the study binders at the two hospital wards when needed. The staff that will include an infant in the study after parental consent is instructed to open the envelope with the lowest number, which will be the top envelope in the binder.

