#### Statistical and sample size calculations

Descriptive statistics will be shown as mean with standard deviation or median with minimum and maximum values for continuous and ordinal variables where appropriate. Number with percent will be shown for categorical variables.

The primary outcome is clinical index at 24 h. The time is chosen since our experience is that most infants will remain at hospital at that time and an effect should have been shown. The effect of the individualised physiotherapy intervention, the non-individualised intervention, and a control group receiving standard care on clinical index at 24 h will be assessed by an ANCOVA model with adjustment for baseline clinical index, and post hoc test for the different group combinations will be performed.

The secondary outcomes, including clinical index at 20 min, will first be assessed by an overall test and if the overall test is shown significant post-hoc tests will be performed. A *p* value below 0.05 will be considered significant for the overall test. Continuous and ordinal variables will be assessed by ANCOVA model with adjustment for baseline values where possible, ANOVA, or Kruskal-Wallis test, with *t* test or Mann-Whitney *U* test as post hoc tests, where appropriate. Categorical variables will be assessed by Fisher’s exact test. Explorative subgroup analyses by gender will be performed. To increase the knowledge about what time the infants will recover, data are collected every 3 h. We will analyse the time the infants recover by means of Fisher’ exact test and Kaplan-Meier analysis. IBM SPSS Statistics 24, or higher, Windows (IBM Corporation, Armonk, NY, USA) will be used to perform the statistical analyses.

The primary analysis will include all participants with available outcome data at 24 h. Drop-outs will not be included in this analysis. A dataset with the imputed values might also be analysed. Simple imputation, mean of the value before and after the missing value or last value carried forward from the assessment three hours earlier, will be performed if data is missing at hour 24 and the patient is still at hospital. If an infant will be discharged from the ward before hour 24, that participant will be excluded from this analysis and will be analysed in the same way as the other potential drop-outs.

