The sample size is calculated on a two-sided two sample *t* test with equal variance. The mean difference that we want to be able to detect in clinical index at 24 h is 2. A previous pilot study (unpublished material) has shown that the standard deviation is approximately 2.8. The power probability for the test is 0.80, and to be able to correct for the three primary tests, comparing the individualised physiotherapy intervention, the non-individualised intervention, and a control group receiving standard care with each other, the type I error probability in the calculation is 0.016, confidence interval 0.95. To be able to detect the difference, 43 evaluable patients in each group is needed. The calculation is performed in SAS Enterprise Guide 6.1 for Windows (SAS Institute Inc., Cary, NC, USA). Incomplete observations and drop-outs are expected to amount to about 20%. Thus, a total of 162 patients are needed to be included in the study. The drop-outs will be analysed according to age, possible viral infection, gender, allocation group, and severity of illness at admission to the ward (saturation, respiratory rate and heart rate or more data if collected). We plan to perform an interim analysis of the data obtained after inclusion of 50% of the estimated sample size in order to check the assumptions about the standard deviation and recalculate the sample size. In that analysis, we will also be able to address possible safety concerns in the study, although we do not anticipate any harmful outcome. That analysis will be performed by a statistician independent of the study, and the result will only be presented to the research group at this stage if any harmful outcome will be detected in the intervention groups, such as significant inferior outcomes in the intervention groups compared to the control arm. Further instructions will be discussed by the trial team before the interim analysis.

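### The primary ANCOVA adjusts only for the baseline clinical index although age is also on record, so the plan may forgo some precision; the model is valid and the sample size stands.

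*Protocol article*

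**What the plan says.** All references are to the protocol article.

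- **Baseline data.** The medical record supplies "gender, age, possible viral agent". The parent interview supplies "heredity for atopic diseases, passive smoking habits, duration of the infection".
- **Inclusion of participants.** Age 0 to 24 months is an entry criterion, so age has to be known for every randomised infant.
- **Statistical and sample size calculations.** The effect on the 24 h clinical index "will be assessed by an ANCOVA model with adjustment for baseline clinical index". No further covariate is named. The same section states: "The drop-outs will be analysed according to age, possible viral infection, gender, allocation group, and severity of illness at admission".
- **Sample size.** "The sample size is calculated on a two-sided two sample" *t* test, with difference 2, SD about 2.8 from an unpublished pilot, and three pairwise comparisons. It adds that "the type I error probability in the calculation is 0.016" and "The power probability for the test is 0.80". This gives 43 evaluable infants per group and 162 in total after about 20% loss.
- **Primary outcome measures, Table 1.** Oral fluid intake carries up to 3 of the 11 index points. For the hour-24 score it is the intake accumulated over the first 24 h in the study. The article states no matching window for the score at study start.

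**The concern.** Adjusting for a variable fixed before randomisation narrows the interval for a treatment contrast when that variable predicts the outcome beyond the covariates already in the model. Age is a natural candidate: the range is wide for this population, the value is known for everyone, and it is measured without assessor judgement.

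The baseline index would usually be expected to carry most of the prognostic information. Here it may carry less than usual. It is a coarse score, and up to 3 of its 11 points have no stated like-for-like value at study start. That leaves room for age to explain something more.

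What is at stake is the width of the three pairwise intervals. Neither the validity of the comparison nor the planned number of infants is in question.

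**Working it through.** **Inputs from the article:** difference 2; SD 2.8; two-sided alpha 0.016 per comparison; 43 evaluable per group, so 3 × 43 = 129; loss about 20%.

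**Inputs assumed, because the article gives none:** partial R² of age given the baseline index, 0 to 0.10; correlation ρ between baseline and 24 h index, 0 or 0.5. The value ρ = 0 stands for the case in which 2.8 is already the SD after baseline adjustment.

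**Step 1: reproduce the plan.** SE = 2.8 × √(2/43) = 0.604. The noncentrality is 2 / 0.604 = 3.312. With 84 degrees of freedom and a critical value of 2.459, the exact two-sample *t* power is 0.801, and 43 is the smallest group size reaching 0.80. Then 43 / 0.80 = 53.75, rounded up to 54, and 3 × 54 = 162. The plan's figures hold, and none of them relies on a covariate.

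**Step 2: planned ANCOVA with the baseline index only.** Error df = 129 − 3 − 1 = 125; residual SD = 2.8 × √(1 − ρ²).

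- ρ = 0: SD 2.800, SE 0.604, power 0.806.
- ρ = 0.5: SD 2.425, SE 0.523, power 0.915.

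**Step 3: add age as one continuous covariate.** Error df = 124. The residual variance is multiplied by (1 − R²). It is also multiplied by about 125/124 = 1.008, the expected price of one more fitted parameter.

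| Partial R² (assumed) | Power, ρ = 0 | Power, ρ = 0.5 |
|---|---|---|
| baseline index only | 0.806 | 0.915 |
| 0 | 0.803 | 0.912 |
| 0.05 | 0.825 | 0.927 |
| 0.10 | 0.848 | 0.941 |

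With ρ = 0, the half-width of the 98.4% interval is 2.442 × 0.604 = 1.475 for the baseline-only model. It becomes 1.481, 1.443 and 1.405 at R² of 0, 0.05 and 0.10.

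**Step 4: break-even.** Age pays for itself when (1 − R²) × 125/124 < 1, that is, when R² > 1 − 124/125 = 0.008, or about 0.01.

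**Step 5: the larger set, for comparison.** Age, duration and viral agent together need about four parameters. The variance price is 125/121 = 1.033, with break-even at R² of about 0.03. With ρ = 0, power is about 0.814, 0.838 and 0.861 at R² of 0.05, 0.10 and 0.15. If the covariates predict nothing, about 1.5 points are lost.

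**The case against.** The strongest reply is that nothing here is wrong. A prespecified ANCOVA on the baseline value of the outcome is standard. The trial was sized on an unadjusted test, so its power does not depend on more covariates, and a separate analysis plan could add them. No figure in the article shows that age predicts the index. All of that stands, and it is why the point is one of possible efficiency at low severity. It does not remove the point, because the article does state its covariate set, and age costs almost nothing to add.

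Objections to the wider covariate set also stand. Duration of infection comes from parents, and a complete-case model would drop infants for whom it is missing. A viral-agent category that merges negative with untested infants is hard to interpret. Neither is a clear choice for the primary model. Site, the factor used for "randomisation in blocks, stratified by the two sites", is likewise not named in the ANCOVA and has a firmer design basis than either; it can be considered in the same edit.

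A reader might infer three stronger things, none of which the article supports:

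- **That precision is certainly being lost.** This needs a partial R² that is not given, and below about 0.01 adding age would slightly widen the intervals.
- **That the plan itself treats age and virus as prognostic, because drop-outs are compared on them.** That list is descriptive. It also contains gender and allocation group, and it omits duration of infection.
- **That adjustment would repair the analysis restricted to infants with 24 h data.** Discharge before 24 h happens after randomisation and reflects recovery. A baseline covariate does not cure bias from excluding those infants.

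**Conclusion.** The point holds as a low-severity refinement: the primary model may forgo some precision by leaving out age.

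For an assumed partial R² of 0.05 to 0.10, the gain is about 2 to 4 power points if 2.8 is the SD after baseline adjustment (0.825 − 0.806 = 0.019; 0.848 − 0.806 = 0.042). It is about 1 to 3 points if 2.8 is the raw SD and the baseline correlation is 0.5 (0.927 − 0.915 = 0.012; 0.941 − 0.915 = 0.026). If age predicts nothing beyond the baseline index, the loss is at most about 0.4 points.

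The figures rest on the assumed R² and correlation, on equal variances, and on 43 evaluable infants in each group. The article does not say whether 2.8 is a raw or an adjusted SD, so both cases are shown.

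**What to change.** In the section Statistical and sample size calculations, before the data are analysed:

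1. Name age (continuous) beside the baseline clinical index as a covariate in the primary ANCOVA.
2. Keep the model with the baseline index alone as a sensitivity analysis.
3. Use duration of infection and viral agent only in a further prespecified sensitivity model. Give it a stated rule that retains infants with missing values, and keep test-negative and untested infants apart.

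The cost is a short addition to the text and one degree of freedom out of 125. No new data are needed and the sample size is unchanged. The timing matters, because a covariate added after the results are known would look data-driven.

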#### Primary outcome measures

A clinical index combining levels of oxygen saturation, oxygen concentration (need for oxygen supplementation), high nasal flow treatment, and oral fluid intake (compared to tube feeding) was constructed; see Table 1. It is possible to achieve a total score between 0 (worst condition) and 11. The primary outcome is a composite index that the research group constructed for this study, based on the factors that determine whether the infant needs hospitalisation [28]. The items in the index were chosen because of their clinical implication. They are based on objective values and are therefore not likely to differ between different assessors. The index has not been validated, but was tested in a small pilot study (unpublished material), where the clinically relevant change of two points was determined by clinical reasoning.

**Table 1 Tab1:** The components of the clinical index used as the primary outcome measure

Outcome	Definition	Measure	Registration time	Score
**Oxygen saturation**	%	By pulse oximetry	At t1, t2, and every subsequent 3rd hour	
	≥ 96			2
	90–95			1
	≤ 89			0
**Oxygen concentration**	%		At t1, t2, and every subsequent 3rd hour	
	21			4
	22–30			3
	31–40			2
	41–50			1
	≥ 51			0
**High nasal flow**	Litres/kg/min		At t1, t2, and every subsequent 3rd hour	
	0			2
	0.1–1			1
	1.1–2			0
**Oral fluid intake**	%^a^	g (weight when breast feeding) or ml (by bottle)	At every feeding session	
	100			3
	51–99			2
	1–50			1
	0			0

^a^Per cent of the calculated daily need

The daily fluid need will be calculated according to nutrition guidelines [29, 30]. The oral fluid intake for analysis at hour 24 will be the collected intake during the first 24 h in the study.

#### Secondary outcome measures

The clinical status of the participants will be assessed by the nursing staff and the parents using the measures in Table 2. Wang score [31] is an observational scale where the nursing staff scores the infants 0–3 where 3 is most severe. The scoring system includes respiratory rate, wheezing, retractions/nasal flaring, and general condition. It has been validated in clinical studies [31–33]. The respiratory rate, retractions, and wheezing is commonly used in studies of bronchiolitis, and the inter-observer agreement is good: 93.1% with a weighted kappa of 0.72 (95% CI 0.66–0.78) [33].

**Table 2 Tab2:** The secondary outcome measures, reported by the clinical staff unless otherwise stated

Secondary outcome	Measure	Registration time
Wang respiratory score [31]		
Respiratory rate	Manual count, per minute. Scale 0–3 where 3 is worst	At baseline, 20 min later and every 3rd hour
Wheezing sound	Clinical observation. Scale 0–3 where 3 is worst	At baseline, 20 min later and every 3rd hour
Retractions/nasal flaring	Clinical observation. Scale 0–3 where 3 is worst	At baseline, 20 min later and every 3rd hour
General condition	Clinical observation. Scale 0–3 where 3 is worst	At baseline, 20 min later and every 3rd hour
General condition (parents’ report)	Observation. Scale 0–10 where 10 is worst	At baseline, 20 min later and every 3rd hour during daytime
Food intake (parents’ report)	Observation. Scale 0–2 where 2 is worst	At baseline, 20 min later and every 3rd hour during daytime
Body weight	Naked weight on scales, g	Once daily
Heart rate	Counts per minute, by pulse-oximetry, probe on the foot	At baseline, 20 min later and every 3rd hour
Time to recovery	Time at hospital, hours	At the end of the study
Lung complications	Referral to intensive care unit—yes/no	At the end of the study

The infant’s food intake will be reported by the parents by a custom-made three-level scale 0–2 where 0 = no self-contained eating at all, 1 = eats less than usual, and 2 = eats as usual. The infant’s general condition will be reported by the parents using a visual numeric rating scale 0–10 where 0 = as usual and 10 = very affected/ill. The numeric rating scale 0–10 has been validated for assessing pain [34], for cancer-related symptoms such as pain and severe tiredness [35], and for postoperative nausea [36] and patient-specific function [37]. It has also been used to assess different symptoms in studies although not validated for this, like well-being, depression, fatigue, and anxiety [38].

Body weight will be used to calculate the daily food/fluid need, and heart rate might show cardiorespiratory load or stress.

Time at hospital and referrals to ICU as a measure of severity of the disease have also been used in other studies [5].

#### Interventions

The position for all infants at baseline is supine on the bed, that is, lying on their backs. Directly following the baseline assessment, there will be 20 min of interventions for the two intervention groups and 20 min of no extra intervention for the controls. All participants will receive the standard care at the ward without limitation, and the participants in the intervention groups will have physiotherapy treatment in addition to the standard care.

*The standard care* at the wards is information to the parents about the importance of fluid intake for their infant, oxygen supplementation, nose drops and suctioning, high nasal flow, inhalations, fluid supplementation, and analgesics, according to need.

The different interventions were chosen based on what is routinely carried out by physiotherapists or nursing staff in hospitals in Sweden [22], including an individualised physiotherapy treatment and a reduced non-individualised treatment. We expect that the individual intervention might be more efficient, but at the same time want to know whether the non-individualised treatment would be sufficient for these patients, indicated by outcomes in the non-individualised group showing a both statistically and clinically relevant improvement compared to the control arm.

In the individualised intervention group, the intervention is minimally given once daily by the physiotherapist, and in the non-individualised intervention group, the intervention is minimally given by the staff once. The randomised treatment, or indeed what will be performed in the control group, will not be monitored, so there might be differences in adherence to the interventions between parents. Our intention, however, is to evaluate the current practice that includes instructions and encouragements to the parents. This attitude is in accordance with a so-called pragmatic RCT, as our intention is to apply the results to the usual care setting [39].

#### Controls

In the control group, the infants will receive no additional body movements, and the parents will not be given extra encouragement to lift up their child.

#### The individualised intervention

The individualised physiotherapy intervention consists of a standardised and individualised programme for 20 min. The individualised intervention will be performed by the physiotherapist once daily, or more often according to his or her judgement. The physiotherapist will lift up the infant in their arms and place the infant in different positions in their arms while bouncing on a large ball; see Fig. 3. The physiotherapist will also stimulate to physical activity by placing the infant in a prone position (lying on their stomach), stimulate the infant to actively move their arms or legs, move the infant’s arms or legs, and supply thoracic compressions, and they may give inhalations and manual cough support on the infant’s belly and chest. The physiotherapist may also suggest other treatments, such as different inhalations or CPAP. They will also teach the parents how to continue this procedure by themselves and will encourage them to do the programme every other hour during the infant’s waking time. The written information to the parents is supplemented in Additional file 3.

**Fig. 3 Fig3:**
[figure not shown]
Example of movement in the individualised intervention group. The physiotherapist bounces on a large ball while holding the infant in different body positions approximately 20 s in each position

#### The non-individualised intervention

The non-individualised intervention can be described as a reduced version of the individualised intervention, without using the large ball, and inhalations given typically only in the upright position, not in frequently changing positions in the arms. The intensity of the treatment will also typically be reduced, as the staff will only have to perform the intervention once, but can choose to repeat it. One member of the clinical staff responsible for the patient at the ward will perform a standardised programme that includes lifting up the infant in their arms to change the body position of the infant, moving the arms and legs of the infant, and giving manual cough support on the belly and chest; see Fig. 4. They will teach the parents to continue to regularly change the infant’s body position themselves. The written information to the parents is supplemented in Additional file 4. The intervention will be performed once at the beginning of the study. The nursing staff can opt to repeat the intervention more times or encourage the parents as often they wish or not at all. All nursing staff at the ward will be trained in the programme. The non-individualised intervention is based on what is commonly performed by the nursing-staff in Swedish hospitals, as instructed by physiotherapists.

**Fig. 4 Fig4:**
[figure not shown]
Example of body position in the non-individualised intervention group, where the nursing staff changes the infant’s body position in their arms

#### Statistical and sample size calculations

Descriptive statistics will be shown as mean with standard deviation or median with minimum and maximum values for continuous and ordinal variables where appropriate. Number with percent will be shown for categorical variables.

The primary outcome is clinical index at 24 h. The time is chosen since our experience is that most infants will remain at hospital at that time and an effect should have been shown. The effect of the individualised physiotherapy intervention, the non-individualised intervention, and a control group receiving standard care on clinical index at 24 h will be assessed by an ANCOVA model with adjustment for baseline clinical index, and post hoc test for the different group combinations will be performed.

The secondary outcomes, including clinical index at 20 min, will first be assessed by an overall test and if the overall test is shown significant post-hoc tests will be performed. A *p* value below 0.05 will be considered significant for the overall test. Continuous and ordinal variables will be assessed by ANCOVA model with adjustment for baseline values where possible, ANOVA, or Kruskal-Wallis test, with *t* test or Mann-Whitney *U* test as post hoc tests, where appropriate. Categorical variables will be assessed by Fisher’s exact test. Explorative subgroup analyses by gender will be performed. To increase the knowledge about what time the infants will recover, data are collected every 3 h. We will analyse the time the infants recover by means of Fisher’ exact test and Kaplan-Meier analysis. IBM SPSS Statistics 24, or higher, Windows (IBM Corporation, Armonk, NY, USA) will be used to perform the statistical analyses.

The primary analysis will include all participants with available outcome data at 24 h. Drop-outs will not be included in this analysis. A dataset with the imputed values might also be analysed. Simple imputation, mean of the value before and after the missing value or last value carried forward from the assessment three hours earlier, will be performed if data is missing at hour 24 and the patient is still at hospital. If an infant will be discharged from the ward before hour 24, that participant will be excluded from this analysis and will be analysed in the same way as the other potential drop-outs.

The sample size is calculated on a two-sided two sample *t* test with equal variance. The mean difference that we want to be able to detect in clinical index at 24 h is 2. A previous pilot study (unpublished material) has shown that the standard deviation is approximately 2.8. The power probability for the test is 0.80, and to be able to correct for the three primary tests, comparing the individualised physiotherapy intervention, the non-individualised intervention, and a control group receiving standard care with each other, the type I error probability in the calculation is 0.016, confidence interval 0.95. To be able to detect the difference, 43 evaluable patients in each group is needed. The calculation is performed in SAS Enterprise Guide 6.1 for Windows (SAS Institute Inc., Cary, NC, USA). Incomplete observations and drop-outs are expected to amount to about 20%. Thus, a total of 162 patients are needed to be included in the study. The drop-outs will be analysed according to age, possible viral infection, gender, allocation group, and severity of illness at admission to the ward (saturation, respiratory rate and heart rate or more data if collected). We plan to perform an interim analysis of the data obtained after inclusion of 50% of the estimated sample size in order to check the assumptions about the standard deviation and recalculate the sample size. In that analysis, we will also be able to address possible safety concerns in the study, although we do not anticipate any harmful outcome. That analysis will be performed by a statistician independent of the study, and the result will only be presented to the research group at this stage if any harmful outcome will be detected in the intervention groups, such as significant inferior outcomes in the intervention groups compared to the control arm. Further instructions will be discussed by the trial team before the interim analysis.

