Block randomisation was chosen to ensure equal numbers of participants in the three groups over time as this can compensate for possible differences in treatment in the two sites, but even for possible changes in the surroundings over time (learning curve, change of staff or temporary severity of the infection). A drawback with equal numbers in the three groups is that exclusions from the physiotherapy intervention group is more likely to be made than from the other groups due to absence of a physiotherapist on occasions, for example at nights and absence due to leave. We have, however, calculated generously on the drop-out rate to compensate for this, and the drop-outs will be closely analysed as described earlier.

There is a need for an easy and clinically relevant scoring system for assessing infants with breathing difficulties in hospitals. Our primary outcome is a clinical index that the research group constructed, based on the factors that determine whether the infant needs hospitalisation [28]. The items in the clinical index were chosen because of their clinical implication. They are based on objective values and are therefore not likely to differ between different assessors. Similar outcome measures were also used by Rochat et al. [9].

For secondary outcomes, we included the Wang score, since it is often used in other studies of infants with acute respiratory infections [5, 8, 19] and has been validated. Furthermore, the parents’ report on the infants’ well-being and eating ability was included. The parents have unique knowledge of their own child, which we thought could make a valuable addition to the nursing staff’s assessment. The parents’ report has not, to our knowledge, been used before in studies of infants with breathing difficulties in hospitals. These two scores were constructed by the research group for this purpose and are not validated for this use. The numeric rating scale 0–10 has been used before to assess different symptoms although not validated for this, like well-being, depression, fatigue, and anxiety [38], and by using it in this study, we hope to gain at least some information about the parents’ assessment of their infant’s general well-being. The outcome measures were chosen with the aim to detect many different types of change in the infants’ status.

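### Allocation is stratified by site, but the primary ANCOVA leaves site out and the plan does not tie its pairwise comparisons to the adjusted model: a small, avoidable loss of precision

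*Protocol article*

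**What the plan says.** All of this is in the Protocol article.

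- **Allocation (Randomisation):** an independent statistician "has performed randomisation in blocks, stratified by the two sites".
- **Reason for blocking (Discussion):** "this can compensate for possible differences in treatment in the two sites".
- **Primary model (Statistical and sample size calculations):** the three-arm effect on the index at 24 h "will be assessed by an ANCOVA model with adjustment for baseline clinical index". Site is not mentioned.
- **Primary pairwise step (same sentence):** "post hoc test for the different group combinations will be performed". The type of test is not given.
- **Secondary outcomes (next paragraph):** "The secondary outcomes, including clinical index at 20 min, will first be assessed by an overall test". The methods are then listed: "Continuous and ordinal variables will be assessed by ANCOVA model with adjustment for baseline values where possible, ANOVA, or Kruskal-Wallis test", followed by "with *t* test or Mann-Whitney *U* test as post hoc tests", with a qualifier at the end of the list: "test as post hoc tests, where appropriate".
- **Sample size:** an unadjusted two-sided two-sample t test with difference 2, SD 2.8, power 0.80 and alpha 0.016 for three primary tests. This gives 43 evaluable per group, and 162 in total after 20% drop-out.

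**The concern.** Blocking within site balances the arms across the two hospitals. That balance makes the treatment comparison more precise, but the analysis shows the gain only if site is in the model. If site is left out, its variation is counted as noise and the reported standard errors are larger than the design warrants. The article itself expects the sites may differ in treatment. Two of the four index components, oxygen concentration and high nasal flow, are treatments that ward staff set, so local practice could plausibly move the score.

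The second gap is the pairwise step. The sample size rests on three pairwise comparisons, so those are the results readers will use. For the primary outcome the article does not say whether they come from the ANCOVA. For secondary outcomes with a baseline value, such as the index at 20 min, no adjusted pairwise test is named at all. A two-group t or Mann-Whitney test after ANCOVA would discard the gain from baseline at the step that compares the arms.

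**Working it through.** **1. The plan's own figure.** Inputs from the article: difference 2, SD 2.8, two-sided alpha 0.016, power 0.80.

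Standard error at 43 per group: 2.8 × √(2/43) = 0.604. Noncentrality: 2/0.604 = 3.31. Degrees of freedom: 84.

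The noncentral t distribution gives power 0.801, so 43 per group is reproduced. With 20% drop-out, 43/0.8 = 53.75, rounded up to 54; 3 × 54 = 162. No covariate enters this calculation.

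**2. Leaving site out.** Let s be the share of residual variance due to site. The article gives no value, so 2% to 10% is assumed. With arms balanced within site, the standard error from the model without site is too large by the factor 1/√(1 − s):

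- s = 0.02: 1/√0.98 = 1.010
- s = 0.05: 1/√0.95 = 1.026
- s = 0.10: 1/√0.90 = 1.054

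This is about 1% to 5%.

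**3. Direction of the error.** An overstated standard error makes rejection harder. A simulation of 129 evaluable infants (3 × 43) used balance within site, site splits of 1:1 and 5:1 (assumed), a baseline-outcome correlation of 0.5 (assumed) and 10,000 null replicates per setting. Type I error of the ANCOVA without site, against nominal 0.016, was:

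| s | Type I error, 1:1 and 5:1 |
|---|---|
| 2% | 0.0150 and 0.0150 |
| 5% | 0.0158 and 0.0120 |
| 10% | 0.0103 and 0.0082 |

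Monte Carlo standard error is √(0.016 × 0.984/10,000) = 0.0013. The results show conservatism as s grows, and no inflation.

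**4. Gain from a baseline-adjusted contrast.** Let ρ be the baseline-outcome correlation (not in the article, assumed). The residual SD becomes 2.8 × √(1 − ρ²). Power is for 43 per group at alpha 0.016, using the same noncentral t as in step 1:

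| ρ | Residual SD | SE of difference | Power |
|---|---|---|---|
| 0 (unadjusted t test) | 2.800 | 0.604 | 0.801 |
| 0.3 | 2.671 | 0.576 | 0.842 |
| 0.4 | 2.566 | 0.553 | 0.873 |
| 0.5 | 2.425 | 0.523 | 0.911 |

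**5. Further gain from site at ρ = 0.5.** The residual SD is 2.8 × √(0.75 × (1 − s)). Power rises from 0.911 to 0.917 (s = 2%), 0.926 (5%) and 0.940 (10%). This is about 0.6 to 3 percentage points.

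**The case against.** The strongest reply is that nothing promised is lost. The trial was sized on an unadjusted t test at alpha 0.016, and that test still delivers 80% power. Adjustment for baseline or site is a bonus. This stands.

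A reader might infer that p values from a model without the stratification factor are invalid. The working does not support this: the error is on the conservative side.

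A reader might also infer that an unadjusted pairwise test answers a different question from the adjusted overall test. For mean differences in a randomised comparison both target the same quantity, and only precision differs.

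It would also go too far to say that the article sends the primary outcome to unadjusted t or Mann-Whitney tests. Those are listed only in the paragraph on secondary outcomes. The primary pairwise step follows directly on the ANCOVA and is compatible with contrasts from it. Even for secondary outcomes, the qualifier "test as post hoc tests, where appropriate" permits reading t as the partner of ANOVA and Mann-Whitney as the partner of Kruskal-Wallis. On that reading no unadjusted test follows ANCOVA, but ANCOVA then has no stated follow-up.

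Finally, this is a condensed article, and a fuller plan could settle the pairwise method. That weakens the point about the unnamed primary test. It does less for the covariates: the article names the covariate of its primary model, and site is not there.

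**Conclusion.** The point holds as one of efficiency and clarity, and it does not threaten validity. Site is a stratification factor and is absent from the stated primary model. The cost is standard errors about 1% to 5% too large if site explains 2% to 10% of residual variance, with type I error at or below nominal and the planned 80% power intact.

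The pairwise point is conditional. It applies to secondary outcomes analysed by ANCOVA, such as the index at 20 min, and only if the t or Mann-Whitney test is used after it. For the primary outcome the test is simply unnamed. Contrasts from the model would secure roughly 4 to 11 percentage points of power above 80% at ρ of 0.3 to 0.5 (0.842 and 0.911 against 0.801).

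The site share and the correlation are assumptions, because the article gives neither. The working also assumes that evaluable infants remain balanced across arms within each site.

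**What to change.** Amend the analysis section in three respects:

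1. Primary model: index at 24 h = arm + baseline index + site.
2. State that the three primary comparisons are contrasts from that model, each tested at the 0.016 level used in the sample size.
3. For continuous secondary outcomes with a baseline value, including the index at 20 min, take pairwise comparisons as contrasts from the corresponding adjusted model. Keep the t and Mann-Whitney tests for outcomes whose overall test is ANOVA or Kruskal-Wallis.

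The cost is a few lines of text and one degree of freedom for site. The sample size does not rise, because 43 per group already assumes no covariate, and SPSS, the package named, can fit the model.
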